**Figure 1 F1:**
[figure not shown]
**Study plan**. 1. Informed consent, baseline assessment (primary and secondary outcomes) and randomisation; 2. Three-month primary outcomes assessment time; 3. Post- intervention assessment time (primary & secondary outcomes); 4. Self- reported use of health services assessment (from month #6 to #9); 5. Follow- up assessment (primary & secondary outcomes).

The interventions are being delivered from Montreal (Québec) with close collaboration with a site-designated nurse for the identification of local community resources. Participants are blind to the underlying hypotheses being tested but cannot be blinded to the intervention. Outcome assessors are blind to group assignment.

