### Detailed description of outcome measures

1. **Unplanned-use of health services and planned-use **is being identified as the number of doctor visits, emergency or medical clinic visits, number of hospitalizations and any other use of other health care professionals (e.g. social worker, psychologist, physical therapist, occupational therapist, etc.) for the 6-month period of the study and an additional six months follow up period. To minimise recall bias, these data are being collected by way of a frequency calendar where each participant notes the health services they used, reasons (e.g. a fall, dizziness, stroke, follow up appointment, physical therapy, etc.) and most importantly if the visit was planned (scheduled) or not (emergency). At the time of data coding, each entry is being scrutinized by three stroke specialist health professionals, not involved in the study, to differentiate noise (such as emergency for a cold or planned-visits for foot care) versus any stroke-related use of the health care system (e.g. emergency for a fall, dizziness, or follow up visit for hypertension or any other risk factors) upon which the program aims to have an impact. Each entry is being dichotomised as either planned for health promotion/prevention or unplanned for a negative event. Using administrative data from each province was considered; however, given the high reliability between self-reported and administrative data of health-services use [40], we chose to rely on self-reported use only. Furthermore, this method of using a calendar has been successfully used with elderly individuals [40]. Given the high prevalence, especially in the early transition period following stroke onset, of stroke recurrence [41], medications errors [42,43]., of falls [44], depressive symptoms [45,46], etc., we estimate a mean number of unplanned-visit equal to three in the first six months post-stroke with a standard deviation of one.

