### Sample size

Because the FITT study in the US was still underway at the time of writing this protocol, sufficient data on the unplanned-use of the health care system was not available. However, considering the high prevalence of stroke recurrence, emergency visits because of medications errors, falls and depression in the stroke population, we estimated a mean number of unplanned-use equal to three in the first six months post-stroke with a standard deviation of one unplanned-use. If we aim to decrease unplanned-use of the health care system by 10%, a sample size of 175 participants in each group is necessary with an alpha level set at 5% (for a bilateral test) and a power of 80%. A sample size of 57 individuals per group would be required to detect a two-point difference in the Quality of Life Index global score using data from a previous study [67] on quality of life of individuals with stroke (n = 72; mean = 20.91 ± 3.8). Given these estimates and considering a potential loss to follow up of 10%, a total sample of **384 individuals **is targeted for recruitment. These numbers are sufficiently large (using same parameters, required n < 65/group for participation and depression) to allow for large effect size of secondary outcomes and to do subgroup analysis according to comorbidity level.

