### Planned statistical analyses

First, baseline characteristics of the sample will be presented using descriptive statistics. All analysis of primary and secondary available outcomes will be realised on an intention-to-treat basis thus respecting group allocation irrespective of whether participants received the intervention or not. The primary endpoint for analysis is the end of the intervention: six months period. A between group comparison on the difference in scores between six months measurement and baseline, between "we call" and "you call" will be made using an independent sample t-test for both primary and secondary outcomes. Effect size of the differences with their 95% confidence interval will be reported. As we anticipate unplanned-use of health services to not be normally distributed (we might end up with many 'zero' negative event), we plan to confirm parametric statistics with non-parametric testing. Also, repeated measures analysis will be realised using the four times of measurements (baseline, three months, six months and one year) where the between-subject factor is the intervention type, the within-group factor is time and their interaction provides the intervention effectiveness, including the one-year follow up phase. Also, multiple linear regression analyses will be used to explore the contribution of the potential explanatory variables (including group assignment, age, gender, living alone versus with a significant other, comorbidity level, *etc*.) on change in primary and secondary outcomes.

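### For unplanned service use, the group-by-time interaction at baseline, 3, 6 and 12 months does not measure effectiveness, and what it shows about persistence depends on a one-year count window that is not stated

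*Protocol article*

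**What the plan says.** - **Analysis.** Under Planned statistical analyses, the protocol article sets six months as the primary endpoint. It then adds that "repeated measures analysis will be realised using the four times of measurements (baseline, three months, six months and one year", with intervention as the between-subject factor and time as the within-group factor. It concludes that "their interaction provides the intervention effectiveness, including the one-year follow up phase". No separate longitudinal method is given for service use.
- **Outcome.** Detailed description of outcome measures, item 1, defines use as numbers of visits and hospital stays, recorded on a calendar "for the 6-month period of the study and an additional six months follow up period".
- **Collection.** The Figure 1 caption lists a step for service use alone between the six-month and final assessments: "Self- reported use of health services assessment (from month #6 to #9".
- **Baseline.** The Design section names quality of life, participation and depression as the baseline measures. The Figure 1 caption speaks more generally of primary and secondary outcomes at baseline.
- **Hypothesis.** The research objective section expects lower unplanned use to last six months beyond the intervention.

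**The concern.** A scale score belongs to a time point; a visit count belongs to an interval. A model indexed by 3, 6 and 12 months has gaps of three, three and six months, so the one-year value has no meaning until its interval is fixed. It could be months 6-12, months 9-12, or everything since baseline.

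Reading the interaction as effectiveness also presumes a common starting level from which the arms diverge. The text describes no such level for service use. Without it, the interaction asks only whether the arm difference changes between post-baseline occasions. That is not the same as whether the intervention works.

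At stake is the persistence hypothesis for a primary outcome. This interaction is the only between-arm test that the article ties to the period after month six. The cost-utility analysis may also draw on later visits, but for costs.

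**Working it through.** **Inputs**
- From Sample size: "mean number of unplanned-use equal to three in the first six months post-stroke with a standard deviation of one unplanned-use"; a targeted reduction of 10%; two-sided 5% and 80% power; "a sample size of 175 participants in each group is necessary".
- Assumed: a constant control rate over the year, so 3 / 2 = 1.5 visits per three months.

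**The plan's own figure.** n = 2 × (1.960 + 0.842)² × 1² / 0.3² = 174.5, rounded up to 175 per group. The stated figure is reproduced.

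**Expected arm differences.** Difference per three-month window = 1.5 × reduction: 0.15 at 10%, 0.075 at 5%, and 0 once the benefit has ended. Differences at 3/6/12 months, control minus intervention:

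| One-year value | Constant 10% | Halved to 5% after month 6 | Ended at month 6 |
|---|---|---|---|
| Raw count, months 6-12 | 0.15/0.15/0.30 | 0.15/0.15/0.15 | 0.15/0.15/0 |
| Count, months 9-12 | 0.15/0.15/0.15 | 0.15/0.15/0.075 | 0.15/0.15/0 |
| Cumulative from baseline | 0.15/0.30/0.60 | 0.15/0.30/0.45 | 0.15/0.30/0.30 |
| Rate per three months | 0.15/0.15/0.15 | 0.15/0.15/0.075 | 0.15/0.15/0 |

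- Raw 6-12 month count: a constant benefit creates an interaction, and a halved benefit creates none. A benefit that ends completely does show.
- Cumulative: the difference from the first six months is carried forward, so an ended benefit still shows at one year.
- Months 9-12, or a rate: no distortion from window length. But a fully persisting benefit then gives no interaction, and the 9-12 count leaves months 6-9 unused.

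**Rejection rates of the interaction test.** Simulated at 175 per arm with a multivariate group-by-time test on the three post-baseline occasions. Normal counts (SD 1/√2 per three months, from the plan's SD of 1) and Poisson counts: independent windows, 4,000 trials. Overdispersed counts: gamma-Poisson with assumed shape 1.5, 3,000 trials.

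| Scenario | Normal | Poisson | Gamma-Poisson |
|---|---|---|---|
| Constant 10%, raw 6-12 | 17.9% | 9.7% | 7.6% and 8.3% (two runs) |
| Constant 10%, months 9-12 | 4.8% | 5.6% | 4.9% |
| Constant 10%, cumulative | 87.4% | 42.1% | 14.3% |
| Halved to 5%, raw 6-12 | 5.2% | 5.0% | 4.4% |
| Halved to 5%, rate per three months | 13.3% | 8.0% | 6.7% (four equal windows) |

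With no effect at any time, rejection stays between 4.8% and 5.4% under each of these readings.

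**The case against.** The strongest reply is that the article fixes neither the one-year window nor the scale, and that a full protocol or analysis plan commonly supplies such detail. This stands in part. A reader might infer that window length drives the interaction and that it misleads in the same way under every reading. The documents do not support that: counts over months 9-12, or a rate, carry no window distortion. What remains is a stated rule, not a gap. The article names the occasions and names the interaction as effectiveness, and with equal windows a constant benefit gives no post-baseline interaction.

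The month 6-9 step may be only an interim calendar pick-up that is later summed. Then it does not contradict the analysis section, and it would be wrong to say that three of the six follow-up months are lost. But summing leads to the 6-12 month or cumulative count, where the distortion occurs.

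The Figure 1 caption could mean that service use is also taken at baseline. If so, the interaction regains some meaning, but the caption and the Design section must be reconciled and the baseline window stated.

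A reader might also expect a large effect on the test. With a 30% reduction and overdispersed counts, a raw 6-12 month window does reject for a constant benefit in about 43% of trials. That is three times the planned effect and is not the plan's magnitude. At 10%, equal windows have little power to detect fading either (6.7% to 13.3% above).

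**Conclusion.** The concern holds in a limited form. For unplanned use, the stated repeated-measures rule does not suit the outcome, and what it says about persistence depends on a window that the article leaves open. At the plan's own 10% effect, fading can look like persistence (0.15/0.15/0.15), and under cumulative counts an ended benefit can look lasting (0.15/0.30/0.30).

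The size is modest. For a constant benefit and a raw 6-12 month count, rejection is about 8-10% against 5% with Poisson or overdispersed counts, and 17.9% with the plan's SD taken as normal. False positives under no effect are not raised. Window length does not touch the six-month primary comparison or the sample size.

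The expected differences assume a constant control rate, while the article itself describes these events as most frequent early. If the later rate were half the early one (0.75 per three months), a constant 10% benefit would give 2 × 0.75 × 0.10 = 0.15 for months 6-12, but 0.075 in each of the two later three-month windows. On raw counts, even equal windows could then make a constant relative benefit look like fading. This is a reason to work with rate ratios.

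**What to change.** For service use only:
- Replace the four listed occasions by the calendar windows 0-3, 3-6, 6-9 and 9-12 months, with no baseline occasion. Reconcile the Figure 1 caption with the Design section on whether use is measured at baseline.
- Fit a log-link count model with an offset for months observed and allowance for within-person correlation.
- Judge effectiveness by the between-arm rate ratio over months 0-6 and persistence by the rate ratio over months 6-12, each with its 95% confidence interval, and not by the interaction on raw counts.

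Keep the repeated-measures model for the scale scores. If a simpler route is preferred, stating the window for each occasion and analysing a rate per three months removes the window distortion. The interaction would still not measure effectiveness, so the arm contrast for months 6-12 should be reported as well.

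The cost is a change of analysis wording. The collection steps already described supply the data, provided that calendar entries can be assigned to their three-month windows.

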### The research objective

The purpose of this study is to assess the effectiveness, for individuals who experience a first "mild" stroke, of a sustainable, low cost, multimodal support intervention (comprising information, education and telephone support) - "***WE CALL***" compared to a passive intervention (providing the name and phone number of a resource person available if they feel the need to) - "***YOU CALL***", on two primary outcomes: unplanned-use of health services for negative events and quality of life. Secondary outcomes include participation level, depressive symptoms, and planned-use of health services for health promotion and secondary prevention. A secondary objective is to *explore *the contribution of potential explanatory variables such as age, gender, living alone versus with a significant other, comorbidity level and access (or not) to a secondary stroke prevention clinic, on outcomes. We hypothesize that the provision of the *"WE CALL" *intervention over the first six months post-stroke, compared to the *"YOU CALL" *will have three positive effects persisting 6 months beyond the intervention period:

1) A decreased unplanned-used of health services for negative events;

2) An improved quality of life;

3) Less depressive symptoms, a better participation in daily activities and social roles, and an increase in planned health visits for promotion and secondary stroke prevention;

In addition, we hypothesize that:

4) Participants with higher comorbidity level will benefit more from the active intervention given the increased complexity of their health status and,

5) Participants with access to secondary stroke prevention (SPC) clinic will benefit more from the intervention than those without SPC access.

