## Methods/Design

### Design

We are conducting a randomized clinical trial, over the first six months post-stroke, with a follow-up at one year (see figure 1). Multi-site recruitment across three Canadian provinces, Québec (Montréal), Ontario (Brantford, Chatham and Kitchener-Waterloo) and Alberta (Calgary), allows a representative sample of participants exposed to different levels of services post stroke such as differing access to Secondary Stroke Prevention Clinics. The target population for this study is all individuals/adults who sustained a first "mild" stroke and who are discharged home within three weeks of being admitted to an acute care hospital. Daily chart reviews of all new stroke admissions are being performed by a site-designated-research-nurse (who is not the treating clinician) to identify potential first mild stroke patients. Potential participants are then approached for further screening. Eligible and interested patients are requested to provide informed consent, and receive a copy of the consent form. Participants are being assessed at baseline (quality of life, participation and depression) in the first month post-stroke by way of a telephone interview. Phone interviews were shown to be as reliable as face-to-face interviews when measuring variables as complex as functional status [36]. They are then being allocated randomly, using stratified block randomization, to one of two groups: 1) "WE CALL" or 2) "YOU CALL". Stratification is done according to level of comorbidity (no or low comorbidity versus high as indicated by a score ≥ 4 on the Comorbidity Index [37]) as this variable is important to the primary outcomes: unplanned-use of health services for negative events and quality of life. Furthermore, to consider the potential effect on outcomes of availability of secondary prevention clinic and urban versus rural areas, parallel randomization (separate randomization) occurs for each province.

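### The group-by-time interaction is named as the measure of effectiveness for every outcome, but service use has no baseline, so a reduction that stays constant would not show in it

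*Protocol article*

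**What the plan says.** Under Planned statistical analyses, the primary endpoint is the end of the six-month intervention, compared between groups by t-test with non-parametric confirmation for unplanned use. A further analysis follows: "repeated measures analysis will be realised using the four times of measurements (baseline, three months, six months and one year"). Its decision rule is that "the within-group factor is time and their interaction provides the intervention effectiveness, including the one-year follow up phase". The rule is not limited to particular outcomes, and the t-test described just before it covers both primary and secondary outcomes.

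Four other places bear on whether the rule fits each outcome:

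- **Design:** "Participants are being assessed at baseline (quality of life, participation and depression) in the first month post-stroke". Service use is not among the measures named.
- **Detailed description of outcome measures:** service use is a calendar count covering the six study months and six further months of follow-up. No period before randomisation is described.
- **Figure 1 legend:** month 3 is labelled "Three-month primary outcomes assessment time", and there is a separate "Self- reported use of health services assessment (from month #6 to #9").
- **The research objective:** the active intervention "will have three positive effects persisting 6 months beyond the intervention period", and the first of these effects is lower unplanned use.

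**The concern.** A group-by-time interaction measures effectiveness when the first time point precedes treatment: the arms start level and then separate. Without such a point, the interaction asks only whether the difference between arms changes from one post-randomisation period to another. A benefit that begins early and holds steady, which is one form of the persistence the protocol hypothesises, then produces no interaction.

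This matters because the repeated-measures analysis is the only stated between-group test that takes in the 12-month phase for unplanned use, a primary outcome. Read literally, it could report no effectiveness where a steady reduction exists, and it would be more likely to reject if the benefit were lost after six months. Switching to the group main effect once the data have been seen would look post hoc.

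**Working it through.** **1. The plan's own figures.** Sample size section: mean 3 unplanned visits in six months, SD 1, a 10% reduction (0.1 × 3 = 0.3), two-sided 5%, power 80%.

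- n per arm = 2 × (1.960 + 0.842)² × 1² / 0.3² = 174.4, so 175, as stated.
- Quality of Life Index, 2 points, SD 3.8: 2 × 7.85 × 3.8² / 2² = 56.7, so 57, as stated.

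**2. The algebra.** Split the follow-up into four quarters, all after randomisation. With a flat rate the control mean is 1.50 per quarter, and a constant effect makes it 1.35 in the active arm. The difference between arms is −0.15 in every quarter. Between any two quarters it changes by (−0.15) − (−0.15) = 0. The interaction is therefore exactly zero, and its rejection rate equals alpha.

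**3. Power on the plan's inputs, 175 per arm.** Assumptions that the document does not supply: the flat quarterly split, and a within-person correlation ρ between quarters of 0 to 0.5. Quarterly variance is set so that the six-month total has SD 1, that is 1 / [2(1 + ρ)]. The 12-month total then has variance 2(1 + 3ρ)/(1 + ρ), and the difference between arms is 4 × 0.15 = 0.6. Power is Φ(0.6/SE − 1.96), with SE = √(2 × variance/175).

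| ρ | Variance, 12-month total | SE | 0.6/SE | Power, 12-month group effect | Simulated group effect | Simulated interaction |
|---|---|---|---|---|---|---|
| 0 | 2.000 | 0.151 | 3.97 | 97.8% | 97% | 4.6% |
| 0.3 | 2.923 | 0.183 | 3.28 | 90.7% | 90% | 5.6% |
| 0.5 | 3.333 | 0.195 | 3.07 | 86.7% | 87% | 5.2% |

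The simulation used 4,000 runs per row with normally distributed quarterly values, and tested the interaction by a multivariate two-group test on the quarter-to-quarter differences. The six-month total rejected in about 80%, in line with Φ(0.3/√(2/175) − 1.96) = Φ(0.85) = 80%.

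**4. Sensitivity, same sample size.**

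- Poisson counts, means 1.5 and 1.35 per quarter: interaction 5.3%, group effect 66%.
- Constant 10% ratio with a falling rate (assumed control quarters 2, 1, 0.75, 0.75): interaction 17% to 47%, six-month total 80% to 81%.
- Effect present only in months 0-6: interaction 35% to 84%.

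The interaction is thus at its weakest when the benefit is steady and stronger when it disappears.

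**5. Quality of life.** With a true baseline, a 2-point difference at every later visit, SD 3.8, assumed correlation 0.5 and 57 per arm, the interaction rejects in 82%. The rule works there.

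**6. Visits by outcome.**

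| Outcome | Times in the Design text and Figure 1 legend | Match to "using the four times of measurements (baseline, three months, six months and one year")? |
|---|---|---|
| Quality of life | Baseline, 3, 6, 12 months | Yes |
| LIFE-H, BDI-II | Baseline, 6, 12 months | No, month 3 is absent |
| Service use | Post-randomisation counts, with an extra collection for months 6-9 | No, baseline is absent and months 6-9 are not listed |

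**The case against.** The strongest reply is that this is an additional analysis. The primary comparison is the six-month test, and the interaction rule does not remove it. That stands. A reader might infer that the trial as a whole would declare an effective intervention ineffective, and the document does not support that. One caveat is that the six-month test is itself worded as a change from baseline, which for service use can only mean a comparison of the six-month counts.

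Second, the four listed times are the quality-of-life schedule, and the interaction is a standard effect test there. This also stands, so striking the sentence altogether would discard a valid rule.

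Third, the Figure 1 legend speaks of "baseline assessment (primary and secondary outcomes) and randomisation", which might be taken to include service use. The Design text names three other measures, and the outcome description counts service use only over the study and follow-up months, so that reading has little support. Coding everyone as zero at baseline would restore power to 69% to 90% in the constant-effect case, but no such coding is stated.

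Fourth, persistence need not mean a constant effect, and the protocol expects events to cluster early. Under a falling rate the interaction keeps some power, so the 5% figure applies to the flat case only.

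Two further inferences should be resisted. One is that unequal windows would create a spurious interaction. The document nowhere says that months 6-12 will be pooled, and with no treatment effect, windows of 3, 3 and 6 months left the rejection rate at 5.3% to 5.5%. The other is that an overall interaction test is an error for quality of life because it does not isolate month 12. A contrast at a given visit is detail that an article may leave to the analysis plan.

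**Conclusion.** The point holds for service use, unplanned and planned, and not for quality of life. As written, the rule measures effectiveness by a quantity that is zero for a constant reduction in a count without a baseline. On the plan's inputs, with an assumed flat rate, constant additive effect and within-person correlation of 0 to 0.5, it rejects in about 5% of trials, against roughly 86% to 98% for the 12-month group effect. The size of the gap depends on those assumptions: it narrows when the rate falls over time, and overdispersed counts would lower the power of the group effect as well. The consequence is confined to the 12-month comparison of service use, for which no other between-group test is stated. The mismatch between the visit list and the Figure 1 legend is a smaller matter of consistency.

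**What to change.** 1. Limit the interaction sentence to outcomes measured at baseline, and keep it for quality of life.
2. For unplanned and planned service use, analyse the post-randomisation counts with a count model, for example negative binomial or GEE with a log-time offset. Report the group rate ratio for months 0-6 and for months 6-12. Use the group-by-period term only to test whether the effect wanes.
3. State the visits used for each outcome and reconcile them with the Figure 1 legend: LIFE-H and BDI-II at baseline and months 6 and 12, and service use by collection period, including months 6-9.

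The cost is analysis wording only. The data are already scheduled, and neither the sample size nor the primary six-month endpoint changes. The amendment should be made before outcome data are examined by arm.

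### Hypotheses 4 and 5 are about effect modification, but no stated analysis names the interaction they need, and the claim that numbers suffice for comorbidity subgroups is wrong for unplanned use

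*Protocol article*

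**What the plan says.** The research objective section of the protocol article states two hypotheses about who gains most. Hypothesis 4 is that "Participants with higher comorbidity level will benefit more from the active intervention given the increased complexity of their health status". Hypothesis 5 is that "Participants with access to secondary stroke prevention (SPC) clinic will benefit more from the intervention than those without SPC access". Neither is restricted to a particular outcome. The same section makes it a secondary objective to explore how age, gender, living situation, comorbidity and clinic access contribute to outcomes.

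The planned statistical analyses section gives t-tests of change with non-parametric confirmation, a repeated measures analysis with a group-by-time interaction, and a regression: "multiple linear regression analyses will be used to explore the contribution of the potential explanatory variables". Its illustrative list puts group assignment and comorbidity level next to each other as separate variables and ends in an open et cetera. Clinic access does not appear in that list.

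The sample size section assumes "a mean number of unplanned-use equal to three in the first six months post-stroke with a standard deviation of one unplanned-use" and a 10% reduction, and concludes that "a sample size of 175 participants in each group is necessary" at two-sided 5% and 80% power. For the Quality of Life Index (QLI) it gives 57 per group for two points with SD 3.8. With 10% loss the target is 384. It then says that these numbers are large enough for the secondary outcomes (fewer than 65 per group for participation and depression) and "to do subgroup analysis according to comorbidity level".

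**The concern.** There are two separate problems.

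**Hypotheses and analysis do not match.** To say that one kind of patient benefits more is to say that the treatment effect differs between kinds of patient. The parameter for that is a group-by-factor interaction. In a regression of change on group plus comorbidity, the comorbidity coefficient says how much more or less the high-comorbidity patients change, averaged over both arms. It carries no information on whether WE CALL helps them more. The same holds for clinic access, if it is entered at all.

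**The sufficiency statement conflicts with the sample size beside it.** If 175 per group is what the whole sample needs for unplanned use, a part of that sample cannot have the same power for the same effect.

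Two of the five hypotheses therefore have no matching stated test. A reader is also told that the trial can support comorbidity subgroup conclusions when, for one of its two primary outcomes, it mostly cannot. A null result in a small stratum could then be taken as absence of benefit.

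**Working it through.** **Inputs.** From the sample size section: mean 3, SD 1, 10% reduction (0.1 × 3 = 0.3 visits, or 0.3 SD); QLI difference 2, SD 3.8; two-sided 5%, power 80%; total 384, loss 10%. From the recruitment section: 1:1 allocation, stratified by Comorbidity Index ≥ 4 versus < 4. Not given: the share with a score ≥ 4. I assume 20% to 50%.

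**Step 1: reproduce the plan's figures.** n per group = 2(1.960 + 0.842)² × SD² / difference².
- Unplanned use: 2 × 7.849 × 1 / 0.09 = 174.4, so 175. Matches.
- QLI: 2 × 7.849 × 3.8² / 2² = 56.7, so 57. Matches.
- Analysable per arm: 192 × 0.9 = 172.8. Whole-sample power for 0.3 visits is then 79%, so nothing is left over to divide.

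**Step 2: power within a stratum.** With share p in the high stratum, n per arm is 172.8p (high) and 172.8(1 − p) (low). Two-sample t-test power for the full design effect is in the table below. As a check at p = 0.5: n = 86.4, SE = √(2/86.4) = 0.152, and 0.3/0.152 − 1.96 = 0.01, so power is about 50%.

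**Step 3: power for the interaction.** The difference between the two stratum effects has SE = SD × √(2/n_high + 2/n_low). Power = Φ(δ/SE − 1.96). The difference detectable with 80% power is 2.802 × SE.
- p = 0.5: SE = √(2/86.4 + 2/86.4) = 0.215. For δ = 0.3, Φ(1.394 − 1.96) = 0.29. Detectable: 0.60 visits.
- p = 0.2: SE = √(2/34.6 + 2/138.2) = 0.269. For δ = 0.3, Φ(1.115 − 1.96) = 0.20. Detectable: 0.75 visits.

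| Share with score ≥ 4 | n per arm, high / low | Unplanned use, 0.3 visits: power high / low | Interaction of 0.3 visits: power | Detectable interaction (visits) | QLI, 2 points: power in high stratum | QLI, 2-point interaction: power |
|---|---|---|---|---|---|---|
| 50% | 86.4 / 86.4 | 50% / 50% | 29% | 0.60 | 93% | 69% |
| 40% | 69.1 / 103.7 | 42% / 58% | 28% | 0.61 | 87% | 67% |
| 30% | 51.8 / 121.0 | 33% / 64% | 25% | 0.66 | 76% | 61% |
| 20% | 34.6 / 138.2 | 23% / 70% | 20% | 0.75 | 58% | 50% |

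**Step 4: sensitivity to loss.** With no loss at all (192 per arm) and an equal split, power for unplanned use is 54% within each stratum and 31% for the interaction.

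**Step 5: size needed.** At an equal split, 80% power for a 0.3-visit interaction needs 4 × 175 = 700 per arm, against 192 recruited.

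**The case against.** **The article is condensed.** The regression list is illustrative and open-ended, and a full protocol or analysis plan may contain product terms. This stands. A reader might infer that the trial cannot answer hypotheses 4 and 5; the document does not support that. It supports only that no analysis stated here tests them.

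**Separate subgroup tests.** A reader might also infer that the plan will test each stratum separately and compare two p-values. The text never says so. It speaks only of subgroup analysis by comorbidity level, which could equally be an interaction test. The method is left open.

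**Exploratory status is largely there already.** Both the secondary objective and the regression sentence use the word explore, and low interaction power is ordinary for exploratory questions. True, and low power alone would not be a finding. But hypotheses 4 and 5 are worded as directional predictions, and the sufficiency sentence claims a capability rather than a caution.

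**The sufficiency sentence may lean on the less demanding outcomes.** Its only support is the figure for participation and depression, and for outcomes needing about 57 to 65 per group a fairly even split does leave enough. This stands for the QLI: 93% within each stratum at an equal split. It would be wrong to call the statement false for every outcome. But it is not limited to those outcomes, nor is hypothesis 4, and unplanned use is a primary outcome.

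**The comorbidity split and the 0.3-visit interaction are the reviewer's choices.** They are. The conclusion for unplanned use holds over the whole assumed range, and the equal split is the most favourable case for the interaction.

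**Conclusion.** The point holds in two parts of different strength.

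The first is a mismatch of wording. Hypotheses 4 and 5 claim differential benefit, and the stated analyses name no group-by-comorbidity or group-by-clinic-access term. An unseen analysis plan could resolve this.

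The second does not depend on any unseen document. The unqualified sufficiency statement is wrong for unplanned use. For the design effect, no assumed split gives both strata more than 50% power, and the high-comorbidity stratum falls to 23% at a 20% share. Power for a 0.3-visit difference in effect is 20% to 29%. The smallest interaction detectable with 80% power is 0.60 to 0.75 visits, two to two and a half times the planned overall effect. For the QLI, within-stratum power is adequate when the high-comorbidity share is 40% or more, and falls short at 30% or less.

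These figures assume the plan's own effect sizes and SDs, the same SD in both strata, 10% loss spread evenly, and a high-comorbidity share of 20% to 50%. The primary comparison, the randomisation and the recruitment target are not affected.

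**What to change.** - In the planned analyses, state that hypotheses 4 and 5 are assessed by group-by-comorbidity-stratum and group-by-clinic-access interaction terms. Report each interaction estimate with its 95% confidence interval.
- State explicitly that both hypotheses are exploratory, in line with the language already used for the secondary objective. Note that clinic access is not randomised and may track site or province, so an interaction with it is open to confounding.
- Limit the sufficiency sentence to the outcomes that support it. Say that for unplanned use the interaction detectable with 80% power is about 0.60 to 0.75 visits, depending on the comorbidity split. A single value of 0.60 would be the best case only.

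The cost is a change of wording and a weaker stated claim for subgroups. Data collection, sample size and randomisation stay as they are.
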